### Sample size

The sample size is calculated based on the significant effects found during the pre-study. In the pre-study, 10,000 handwashing events were recorded over a period of 42 days in a treatment group (n = 82 children in two clusters) and a control group (n = 53 children in two clusters). Using Cohen’s power analysis with f^2^ = 0,35 (large effect size) and power level of 0.8 and 2 predictors and a probability level of 0.05 leads to n = 31. However, since randomization is on a cluster level, the n must be increased. With the ICC from the pre-study of 0.062, and estimated cluster size (size of each kindergarten) of 40 children, we calculate the design effect:

D=1+(m−1)*ICC=1+(40−1)*0.062=3.418

Thus, we need to increase the sample size by 3.418 compared to individual randomization, due to cluster randomization leading to 106 participants (n = 31 * 4.418 = 106). With the assumption of a cluster size of 40 children per kindergarten, this leads to three kindergartens that need to participate in the study. Each kindergarten represents one cluster and gets assigned to be the control, the intervention A, B, and C groups. Two intervention groups will be covered by one cluster.

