## Abstract

Early implementation of interventions at a young age fosters behaviour changes and helps to adopt behaviours that promote health. Digital technologies may help to promote the hand hygiene behaviour of children. However, there is a lack of digital feedback interventions focusing on the hand hygiene behaviour of preschool children in childhood education and care settings. This study protocol aims to describe a study that evaluates the effectiveness of a gamified live feedback intervention and explores underlying behavioural theories in achieving better hand hygiene behaviour of preschool children in early childhood education and care settings. This study will be a four-arm cluster randomized controlled trial with three phases and a twelve-month follow-up by country stratification. The sample size is 106 children of which one cluster will have a minimum number of 40 children. During the baseline phase, all groups will have automated monitoring systems installed. In the intervention phase, the control group will have no screen activity. The intervention groups will have feedback displays during the handwashing activity. Intervention A will receive instructions, and intervention B and C groups will receive instructions and a reward. In the post-intervention phase, all the groups will have no screen activity except intervention C which will receive instructions from the screen but no reward. The outcome measures will be hand hygiene behaviour, self-efficacy, and intrinsic motivation. Outcome measures will be collected at baseline, intervention, and post-intervention phases and a 12-month follow-up. The data will be analysed with quantitative and qualitative methods. The findings of the planned study will provide whether this gamified live feedback intervention can be recommended to be used in educational settings to improve the hand hygiene behaviour of preschool children to promote health.

The trial is registered with ClinicalTrials.gov (registration number NCT05395988
https://clinicaltrials.gov/ct2/show/NCT05395988?term=NCT05395988&draw=2&rank=1).

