### Data analyses

Data will be analysed using qualitative and statistical methods. All eligible participants will be included in the analysis. The statistical analyses will be performed with R. The categorical and numerical data will be analysed using one-way analysis of variance (ANOVA). Qualitative analysis will be presented thematically [42].

For the measurement data from the system:

Data pre-processing: Data will be investigated where water and soaping data are combined to single handwashing procedures. Data points that are not valid (outside of kindergarten opening hours) will be removed. The descriptive statistics of the clusters, randomization checks, ICC (intracluster correlation) will be calculated. The data will be analyzed using linear fixed-effect regression model for panel data, and dependent variable soaping time. The four groups will be compared in baseline, intervention, and post-intervention phases.

For the survey and staff interview data:

The comparison among the groups will be implemented using random effects regression, allowing for the clustered nature of the data, and adjusted using the covariates of the adjusted analyses (when a small number of clusters are present) [43]. Simple bias analysis will be used to quantify the uncertainty of the biases such as confounding variables [33]. The qualitative results of the survey and kindergarten staff interview will be analysed and compared thematically. The four groups will be compared after intervention phase.

For the children interview and observation data:

The analyses will be compared among groups based on the complete data only. The comparative analyses approach used to calculate the observation, survey, and staff interview will be used. The self-efficacy measurement scale will be developed and evaluated for its psychometric properties [44,45]. The qualitative result of the observation and interviews will be analysed and compared thematically [42]. Children who will participate the interview at one time point will be considered as missing data, these will be excluded from the analysis. The four groups will be compared in baseline, intervention, and post-intervention phases.

For the sickness day data:

The total sick leave days are compared among the groups one year before and after the start of the baseline phase.

The statisticians of the two universities will validate the statistical results of the data.

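### The sample-size section misprints its multiplier (4.418 for 3.418, leaving 106 unchanged) and, separately, uses 2 undefined predictors, so 80% power at 106 children does not cover the four-group comparison (about 73% with three group terms)

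*Protocol article*

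**What the plan says.** The Sample size section starts from a regression power calculation, "Using Cohen’s power analysis with f^2^ = 0,35 (large effect size", and continues with "power level of 0.8 and 2 predictors and a probability level of 0.05 leads to n = 31". It does not name the two predictors.

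It then allows for clustering "With the ICC from the pre-study of 0.062" and an "estimated cluster size (size of each kindergarten) of 40 children", which gives "D=1+(m−1)*ICC=1+(40−1)*0.062=3.418". The next sentence repeats 3.418 as the inflation factor, but the product is printed with a different multiplier: "due to cluster randomization leading to 106 participants (n = 31 * 4.418 = 106". From 106 children and 40 per kindergarten the section derives three kindergartens, and it adds that one cluster will cover two of the intervention groups. The Abstract carries the total forward: "The sample size is 106 children of which one cluster will have a minimum number of 40 children".

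The Trial design section describes four arms. The Data analyses section says, for the sensor data and again for the child interviews and observations, "The four groups will be compared in baseline, intervention, and post-intervention phases". Under Hypotheses, H1 and H4a set B and C together against A, whereas H2, H3a and H4b each state a difference between B and C.

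**The concern.** There are two distinct problems in one short derivation.

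The line that yields the headline total does not multiply out, and its multiplier contradicts the design effect printed just before it. A reader cannot tell from that line alone whether the multiplier or the total is wrong.

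The number of predictors does not match the design. A four-level group factor takes three indicator terms before any phase, country or covariate term. A calculation with two terms is a calculation for at most three groups. If the 80% figure is read as applying to the four-group comparison that the analysis section announces, it is too favourable, and the arm contrast left out is the one between B and C on which several hypotheses depend.

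**Working it through.** **Inputs.** From Sample size: f² = 0.35, α = 0.05, power 0.80, u = 2 predictors, ICC = 0.062, m = 40. From Trial design and Data analyses: four groups, hence u = 3 group terms.

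**Method.** Overall F test in multiple regression. Power = P(F′ > F₀.₉₅(u, v)), where F′ is noncentral F with u and v = n − u − 1 degrees of freedom and noncentrality λ = f²·n. Find the smallest n with power of at least 0.80 and multiply by D = 1 + (m − 1)·ICC. For a given number of children N, use effective n = N/D.

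**Step 1: reproduce the plan (u = 2).**
- n = 30 gives 78.9%; n = 31 (v = 28, λ = 10.85) gives 80.4%. So n = 31, as stated. The alternative λ = f²·v gives n = 34, so it is not the formula the plan used.
- D = 1 + 39 × 0.062 = 3.418, as stated.
- 31 × 3.418 = 105.96, so 106, as stated.

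**Step 2: the printed product.** 31 × 4.418 = 136.96, not 106. The stated design effect gives 106 and the printed multiplier does not, so the slip is in the multiplier.

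**Step 3: three group terms (u = 3), other inputs unchanged.**
- n = 36 (v = 32, λ = 12.6) gives 81.0%; n = 35 gives 79.6%. So n = 36.
- 36 × 3.418 = 123.05, so 124 children.

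**Step 4: power at the planned numbers.**

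| Children | Cluster size | D | Effective n | u = 2 | u = 3 |
|---|---|---|---|---|---|
| 106 | 40 | 3.418 | 31.0 | 80.4% | 73.2% |
| 120 (three × 40) | 40 | 3.418 | 35.1 | 85.8% | 79.7% |

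**Step 5: dependence on cluster size.** D = 3.418 belongs to m = 40.
- 106 children in three kindergartens: m = 35.3, D = 3.13, effective n = 33.9, power 77.9% (u = 3).
- 106 children in four kindergartens: m = 26.5, D = 2.58, effective n = 41.1, power 86.9%.
- 124 children in four kindergartens: m = 31, D = 1 + 30 × 0.062 = 2.86, effective n = 124/2.86 = 43.4, power 89.0%. At that cluster size the formula asks for only 36 × 2.86 = 102.96, so 103 children.

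The 124 in Step 3 therefore must not be paired with four kindergartens. Four kindergartens of 40 would be 160 children.

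**The case against.** The best defence of 2 predictors is H1. During the intervention phase B and C receive the same content, so there are three distinct conditions: no display, instruction, and instruction with reward. Two indicators, one for the display and one for the reward, code these exactly, and H1 is worded that way. The remark that one cluster covers two intervention groups may point in the same direction. This stands as far as it goes: the article does not define the predictors, so reading them as codes for all four groups is an inference. It does not rescue the calculation for the four-group comparison or for H2, H3a and H4b, and the article nowhere limits the 80% to H1.

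The size of the shortfall can also be disputed. If three kindergartens of 40 are filled, 120 children give 79.7%, which is 0.3 percentage points below target. That stands. But the stated figure is 106 children, and keeping f² at 0.35 with a third term is itself an assumption.

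Two stronger readings are tempting, and the document supports neither. A reader might infer that 106 children give only 73% on the plan's own assumptions. Those assumptions include 2 predictors and give 80.4%; the 73% arises only when 2 becomes 3. A reader might also infer that the misprint lowers the power or invalidates 106. It does neither, because the total was computed with 3.418.

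**Conclusion.** Both errors hold, independently of each other. The multiplier 4.418 is a misprint for 3.418 with no effect on the target. The 80% power claim at 106 children does not extend to the four-group comparison: with three group terms it is about 73% at 106 children and about 79.7% at 120, and 124 children would be needed in clusters of 40.

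This rests on f² staying at 0.35 for three terms, on ICC 0.062 and clusters of 40 as stated, and on the claim being meant for all four groups. If the 2 predictors were meant for the three conditions of H1, the calculation is internally correct for H1 and the fault is that it neither says so nor covers the B-versus-C hypotheses.

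All the figures count children with a simple design effect. They do not deal with having about one kindergarten per arm, which is a separate and larger problem. Neither 80% nor 73% should be read as the real power of the trial.

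**What to change.** In Sample size:
1. Replace 4.418 with 3.418. The total of 106 in that section and in the Abstract needs no change on this account.
2. State what the 2 predictors are and which hypothesis they serve.
3. Then do one of two things. Either restate the power for the four-group comparison with three group terms (about 73% at 106 children, about 80% at three full kindergartens of 40), or state that the 80% applies only to the three-condition comparison in H1 and that the B-versus-C hypotheses were not powered.

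Do not replace the target with 124 children in four kindergartens, because that combines a design effect for clusters of 40 with clusters of 31. If the number of kindergartens changes, recompute D for the new cluster size.

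The cost is wording only: no change to recruitment, allocation or data collection. The stated power becomes less favourable or its scope narrower. Whichever figure is kept should carry a note that it does not account for the number of kindergartens per arm.

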### Data management

The anonymity of the participants using the faucets will be preserved as no person-specific data is collected. The experimental setup and data collection will not allow the collection of personal data and draw conclusions about the individuals. However, since this study will be a cluster randomized trial, the data collected will be the summary data for each arm. In addition, consent will be asked for the collection and storing of the observation, survey, interview, and sick leave data from the participating children, parents, and kindergarten staff. The behavioural data of the experiments will be stored in associated databases. All the data CSV files will be used anonymously. The data collected will be stored in both universities.

Research results will only be published in an anonymized form that does not allow conclusions to be drawn about each child. To ensure that behavioural data is protected from being captured by a third party, access to all critical infrastructure services will require authentication and authorization. In case a third party steals a faucet, the faucet’s access to the server will be remotely disabled. The documentation and the software components will be stored in git-repositories which have a version control functionality. The data communication and data storage will comply with GDPR accordingly.

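### The 106 children and 80% power are not in the unit of the primary sensor analysis, and three kindergartens for four arms leave no basis for a power claim

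*Protocol article*

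**What the plan says.** The Sample size section of the protocol article starts from a regression power analysis: "Using Cohen’s power analysis with f^2^ = 0,35 (large effect size"), with "power level of 0.8 and 2 predictors and a probability level of 0.05 leads to n = 31". It then adjusts for cluster randomization: "With the ICC from the pre-study of 0.062, and estimated cluster size (size of each kindergarten) of 40 children", so that "D=1+(m−1)*ICC=1+(40−1)*0.062=3.418", "leading to 106 participants (n = 31 * 4.418 = 106"). At 40 children each, it concludes that three kindergartens are needed, with one of them covering two intervention groups. The Abstract repeats the total: "The sample size is 106 children".

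The same section describes the pre-study by its sensor yield, "10,000 handwashing events were recorded over a period of 42 days", from 82 treated and 53 control children in four clusters.

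Elsewhere the primary outcome is a sensor measurement. Outcome measures derives it from water and soap signals at the basin. Data analyses joins those signals into one record per wash and fits a linear fixed-effect panel regression to soaping time. Data management states: "The anonymity of the participants using the faucets will be preserved as no person-specific data is collected". It adds that the data will be summaries by arm.

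**The concern.** Sample size, design effect and power must count the same thing as the analysis they support. Here n and m count children, whereas the model receives washes, or some aggregate of washes by basin or day. No child value can be formed from the sensor data, so the child count never enters the primary model.

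The 106 does appear to be meant for the primary outcome. The section rests it on the pre-study's significant effects, and Limitations reports the pre-study's main result as longer handwashing time. It is hard to read the figure as sized for self-efficacy, because that scale is still to be developed.

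A reader will take 80% power as a property of the primary between-arm comparison and will assume that enrolling 106 children secures it. Neither follows from the calculation shown.

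**Working it through.** **Inputs.** From Sample size: f² = 0.35, 2 predictors, alpha 0.05, power 0.8, ICC 0.062, m = 40 children, three kindergartens; pre-study totals of 10,000 events, 42 days, 82 + 53 = 135 children and 4 clusters. From Implementation: three weeks (21 days) per phase. Not stated: the level of the ICC, the unit of the panel, and which fixed effects are fitted.

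**1. The plan's own figure.** For the overall F test with u = 2, v = n − 3 and non-centrality f²·n, the smallest n with power of at least 0.80 is 31 (power 0.804). The design effect is 1 + 39 × 0.062 = 3.418. Then 31 × 3.418 = 105.96, or 106, and 106/40 = 2.65, or three kindergartens. The printed multiplier 4.418 would give 31 × 4.418 = 137, so it is a misprint and 106 comes from 3.418. The arithmetic reproduces; the unit is what fails.

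**2. The effect size also depends on the unit.** f² = 0.35 means R² = 0.35/1.35 = 0.26. A share of variance explained among child means is not the same quantity as a share explained among single washes.

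**3. If 0.062 is an ICC of events.** Assume the pre-study rate carries over: 10,000/(135 × 42) = 1.76 events per child per calendar day. Forty children over 21 days then give 1.764 × 40 × 21 ≈ 1,481 events per kindergarten per phase. With D = 1 + (1,481 − 1) × ICC:

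| ICC (events) | D | Events needed (31 × D) | Kindergartens' worth |
|---|---|---|---|
| 0.01 | 15.8 | 490 | 0.33 |
| 0.062 | 92.8 | 2,876 | 1.94 |
| 0.10 | 149 | 4,620 | 3.12 |

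If the panel unit were the kindergarten-day, 21 per phase at the same ICC would give D = 1 + 20 × 0.062 = 2.24. An ICC of daily aggregates would differ from one of washes, so this shows only how far the answer depends on a unit that the article does not name.

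**4. Effect of the unit change alone, at ICC 0.062.** On the child scale, three kindergartens give 120/3.418 = 35.1 effective observations and nominal power 0.86. On the event scale they give 3 × 1,481/92.8 = 47.9 and nominal power 0.95. The substitution does not make the nominal power worse.

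**5. Cluster-level degrees of freedom.** The nominal powers in step 4 count error degrees of freedom as if effective observations were independent. Counted in kindergartens, error df = k − u − 1:

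- three kindergartens with the two stated predictors: 3 − 2 − 1 = 0;
- four kindergartens, one per arm, with three arm contrasts: 4 − 3 − 1 = 0;
- three kindergartens with three arm contrasts: 3 − 3 − 1 = −1.

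With zero or negative error df the between-arm test does not exist, so no power can be computed. As an illustration with f² = 0.35, ICC 0.062 and three arm contrasts, six kindergartens give power 0.37 on the child scale and 0.46 on the event scale; eight give 0.83 and 0.92. At these counts, the number of kindergartens matters far more than the choice of unit.

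**The case against.** The strongest reply is that the event-scale design effect does not fit the primary model either. If the fixed effects are for kindergarten or basin, stable differences between kindergartens drop out of the baseline-to-intervention change, and 1 + (m − 1) × ICC no longer applies. This stands: the values near 93 are conditional and cannot be offered as the right design effect. It does not restore the power. Each kindergarten still contributes one change per phase contrast, and three such changes cannot estimate four arms and an error term.

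A reader might infer that a design effect of 93 instead of 3.418 makes the trial many times too small. The documents do not support this. A kindergarten supplies far more events than children, and at the same ICC the requirement falls from 2.65 to about 1.94 kindergartens.

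A reader might also infer that 0.062 must be an ICC of events because the pre-study tested this technology. That is plausible but undocumented, since the article never says how it was calculated. Nor does it follow that the number of children is irrelevant to precision. Lack of identifiers prevents modelling of clustering by child but does not remove it, and a kindergarten's mean soaping time may still depend on how many different children wash. Children do generate the events; the records simply cannot be assigned to them.

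Finally, an article may leave the level of an ICC to the full protocol or SAP. That is fair for the ICC. It does not cover a stated size and power whose unit conflicts with the analysis described in the same article.

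**Conclusion.** The figure is wrong as written. 106 children with power 0.8 is internally reproducible but is not in the unit of the primary analysis, and the power it carries does not describe that analysis. This rests on the Data management statement about anonymity and on the per-wash records in Data analyses, not on any assumption about the ICC.

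No single replacement figure can be given. The design effect of about 93 assumes that the ICC is of events, 1.76 events per child-day, and no allowance for the between-phase contrast. It is not evidence that more children are needed.

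The power claim itself fails for a separate reason: at the stated three kindergartens for four arms, no cluster-level error degrees of freedom remain. This holds whichever unit is chosen.

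**What to change.** - Withdraw 106 children with power 0.8 as the primary-outcome figure in Sample size, and reword the Abstract to match.
- Name the unit of n and of the ICC, and reconcile Sample size with Data analyses and Data management.
- Restate the size as kindergartens per arm and events (or basin-days) per kindergarten per phase. Use the pre-study ICC at that level and its between-phase correlation, with cluster-level degrees of freedom.
- Report the power that the available kindergartens give, or say that none can be claimed.
- If 106 is kept, describe it only as a recruitment target without a power claim. The article gives no effect size or ICC for the interview outcomes that would support one.

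The cost is a recalculation from pre-study data the team should already hold, and loss of the stated power claim. The restatement itself requires no extra enrolment.

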**Fig 1 pone.0280686.g001:**
[figure not shown]
Schedule of enrolment, intervention, and assessments.

This study will be a four-arm cluster randomized controlled trial study with three phases and a twelve-month follow-up by country stratification. This study will evaluate the effectiveness of the gamified live feedback intervention on children’s handwashing behaviour, self-efficacy, and motivation in three different phases: the baseline, intervention, and post-intervention phases. In Finland, there will be a twelve-month follow-up after the baseline phase. This study will consist of four groups, the control group, and three different intervention groups. All the groups will have automated monitoring systems installed before the start of the baseline phase and will be available in all phases. The system will be de-installed after the post-intervention phase.

During the baseline phase, all the groups will have no screen activity. During the intervention phase, the control group will have no screen activity. The intervention A group will have a screen display providing handwashing instructions but no reward, and the intervention B and C groups will receive handwashing instructions and rewards from the screen display. During the post-intervention phase, all the groups will have no screen activity except the intervention C group which will receive handwashing instructions but no reward (Fig 2).

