**Fig 2 pone.0280686.g002:**
[figure not shown]
The design and data collection of the study.

The design of this study is cluster randomized controlled, where one kindergarten serves as one cluster. Clustering will be used since the hand hygiene intervention is designed to be installed in certain areas to be used in groups. Kindergartens will be assigned as clusters rather than individuals to minimize the potential contamination among the groups, and to more accurately follow the process that will be taken at scale [33,34].

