### Randomization

The cluster randomization will be at the kindergarten level. Kindergartens will be randomly assigned to control or intervention groups by two researchers that are not members of the research team and are stratified by country. One kindergarten serves as one cluster. Simple randomization will be used which will be drawing lots, where each cluster will be assigned a number in a piece of paper. The parents will enrol their children for participation in the study within the time set through the website link provided and email.

No information will be given regarding the allocation. Allocation will be about four weeks before the start of the baseline phase and will be conducted by the two non-member researchers. They will generate the allocation sequence, enroll the participants, and assign them to control or intervention groups. There will be complete concealment of the allocation from the members of the research team and the participants, to exclude the possibility of predicting the next allocation [33].

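### Three kindergartens for four arms leave no replication at the randomised level, so the stated 0.8 power does not hold for any comparison between kindergartens

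*Protocol article*

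**What the plan says.** All places are in the Protocol article.

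- **Sample size.** The calculation takes Cohen's f² = 0.35 and a "power level of 0.8 and 2 predictors"; with alpha 0.05 this gives 31 individuals. An ICC of 0.062 and 40 children per kindergarten give a design effect of 3.418 and a total of 106 children. The section concludes that "this leads to three kindergartens that need to participate in the study" and adds: "Two intervention groups will be covered by one cluster".
- **Trial design.** "This study will be a four-arm cluster randomized controlled trial study with three phases and a twelve-month follow-up by country stratification". On the choice of unit: "Kindergartens will be assigned as clusters rather than individuals to minimize the potential contamination among the groups".
- **Randomization.** Allocation is by kindergarten and stratified by country. "Simple randomization will be used which will be drawing lots".
- **Implementation and Data collection.** Sensor data run through three-week baseline, intervention and post-intervention phases. The parent survey is taken once, at the end of the intervention phase. Staff are interviewed then and again just after the post-intervention phase begins. Sick leave is tracked in Finland only.
- **Data analyses.** Sensor data go into a fixed-effect panel regression on soaping time. Survey and staff data go into a random-effects regression. One-way ANOVA is named as a general method.

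**The concern.** A design effect turns an individual sample size into a clustered one only if each arm contains several clusters, so that variation between clusters can be estimated and averaged out. Here the number of clusters is smaller than the number of arms. A difference between arms in different kindergartens may then be an ordinary difference, or an ordinary change, in one kindergarten.

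Most of the hypotheses rank the arms against each other, and the stated aim is to judge effectiveness. If the protocol promises 80% power for comparisons that have no valid error term, nominally significant results would be read as evidence for the display when they may reflect only which kindergarten was drawn.

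**Working it through.** **1. The plan's own figure.** Inputs from Sample size: f² = 0.35, alpha 0.05, power 0.8, 2 predictors, ICC 0.062, m = 40.
- Noncentral F with noncentrality f²·N: the smallest N with power of at least 0.80 is 31 (power 0.804).
- D = 1 + 39 × 0.062 = 3.418, and 31 × 3.418 = 105.96, i.e. 106.
- 106 / 40 = 2.65, i.e. 3 kindergartens.

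The figure reproduces. The printed multiplier 4.418 is a misprint, since 31 × 4.418 = 136.96.

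**2. Degrees of freedom at the randomised level.** Three kindergartens with two arms sharing one make three cluster-level conditions on three clusters: 3 − 3 = 0. With one kindergarten per arm: 4 − 4 = 0. In both layouts the variance between kindergartens cannot be estimated separately from the arm effects, by a random-effects model or otherwise. No power can be attached to a cross-kindergarten contrast.

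**3. Outcomes without a baseline (parent survey, staff interview).** Assumption: the pre-study ICC of 0.062 applies to them. Forty responses per kindergarten fits the parent survey at best; the number of staff is not given. In units of the outcome SD:
- Variance of one kindergarten mean = 0.062 + 0.938/40 = 0.08545.
- SD of the difference between two identically treated kindergartens = √(2 × 0.08545) = 0.413; 95% range ±1.96 × 0.413 = ±0.81.
- With unlimited children: √(2 × 0.062) = 0.352; range ±0.69.
- Standard error if clustering is ignored = √(2 × 0.938/40) = 0.217. The two-sided 5% cut-off on 78 df is 1.99 × 0.217 = 0.431. Then 0.431/0.413 = 1.04, and a null difference exceeds it about 30% of the time.
- A one-way ANOVA across three such kindergartens rejected in about 43% of 20,000 simulated null data sets.

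**4. Sensor outcome, with baseline.** The change-from-baseline contrast removes stable differences. With unlimited children its 95% range under no effect is ±1.96 × √(4 × 0.062 × (1 − r)), where r is the correlation of a kindergarten's level between two phases. The documents do not give r. Assumed values give:

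| r | 95% range (SD) |
|---|---|
| 0.5 | ±0.69 |
| 0.8 | ±0.44 |
| 0.9 | ±0.31 |

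**5. The shared kindergarten.** The two arms in it are compared within one building, so kindergarten cancels. But they are not separately assigned by kindergarten, as Randomization requires, and children under different conditions mix, which the Trial design rationale was meant to prevent. Even a B and C pairing, identical during the intervention phase, diverges afterwards: C keeps a screen and B does not.

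**6. Country.** If three is the total and both countries take part, the split is two and one. The country with one kindergarten holds at most two arms. Finland has at most two kindergartens and so at most three arms, counting the shared pair. The sick-leave comparison cannot contain four separately randomised arms.

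**7. What replication would give (illustration).** Cluster-mean comparison of two arms without baseline, c kindergartens per arm, df = 2(c − 1), no multiplicity or country adjustment. If f² = 0.35 is read as an equal two-group contrast, d = 2√0.35 = 1.18.

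| Assumed d | c per arm | Total | Power |
|---|---|---|---|
| 1.18 | 2 | 8 | 57% |
| 1.18 | 3 | 12 | 95% |
| 0.8 | 4 | 16 | 89% |
| 0.5 | 7 | 28 | 84% |

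**The case against.** The strongest reply is that the design has its own protection. Every kindergarten has a three-week baseline, and the panel model compares phases within kindergarten. Country, usual routine, stable staffing and age mix therefore drop out of the sensor analysis, provided the fixed effects are at kindergarten level or finer. The child interviews and observations also have a baseline measurement. H3b and H3c are partly statements about an arm against its own baseline and need no cross-kindergarten contrast.

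This stands, and it rules out a stronger reading. A reader might infer that every arm effect is inseparable from kindergarten and that no analysis can help. The documents do not support that: stable differences are removable for outcomes with a baseline, and the contrast between the two co-located arms is not confounded with kindergarten at all. The ±0.81 SD likewise must not be applied to the panel analysis. What the baseline cannot do is create replication. An outbreak, a staffing change or fading novelty in one kindergarten still looks like an arm effect.

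Three further inferences go too far:
- Counting 3 − 4 = −1 degrees of freedom overlooks the shared cluster; the figure is 0.
- Eight kindergartens are a minimum only if every arm must appear in both countries, which the text does not say.
- Defining a kindergarten as one cluster is not itself contradicted by placing two arms in it. The conflict is with kindergarten-level assignment and the contamination rationale.

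Finally, three may be a minimum, and the randomisation flowchart (Fig 8) is not available here. But the text gives no larger number, the 0.8 is derived for three, and the sharing sentence makes sense only with fewer clusters than arms.

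**Conclusion.** The point holds for contrasts across kindergartens, which include every arm versus control. The arithmetic to 106 is sound; the step from 106 children to three clusters for four arms, with 0.8 power attached, is not. The power claim fails whatever the ICC, because it fails on degrees of freedom.

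The consequence differs by outcome. For the parent survey and staff interview, arm and kindergarten are fully confounded, with chance differences up to about 0.8 SD (0.7 SD however many respond) if the pre-study ICC carries over. For the sensor outcome only kindergarten-specific change is confounded with arm; its size depends on a between-phase correlation that the documents do not give. For the two co-located arms the problem is contamination. The country and sick-leave consequences hold only if three is the total enrolled.

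**What to change.** - **Power.** Withdraw the 0.8 statement, or replace it with cluster-level power for the number of kindergartens actually allocated per arm, with the between-cluster degrees of freedom shown.
- **Reporting.** While any arm rests on a single or shared kindergarten, report cross-kindergarten contrasts as descriptive estimates, not tests. State that arm is confounded with kindergarten-specific change, and with kindergarten itself where there is no baseline.
- **Shared cluster.** Reconcile the sentence on two arms in one cluster with the Trial design and Randomization sections. Either justify the sharing and say which arms share, or give each arm its own kindergarten.
- **Country.** State how many kindergartens per country are to be allocated, and which arms the Finland-only sick-leave comparison can contain.

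**Cost.** The first two changes and the country statement are wording. One kindergarten per arm needs at least four, i.e. at least one more to recruit and equip, and still leaves 0 error degrees of freedom; tests need replication beyond that. The stated power is lost or becomes less favourable, and the between-arm conclusions are weaker.
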